#### Statistical analysis

Statistical analyses will be performed using the statistical software package SPSS 19.0 (SPSS Inc, Chicago, IL). Two-sided tests using the 5% critical level will be used throughout. The Mann–Whitney U test will be used to determine a significant difference in transfusion needs between the 2 groups. Intergroup categorical data will be compared using Chi-square or Fisher exact test. Intergroup continuous data will be analyzed with parametric or non-parametric analysis methods depending on the presence/absence of Gaussian distribution. If required, appropriate corrections for multiple comparisons will be applied. Independent risk factors for bleeding diathesis and transfusion during OLT will be identified using uni- and multivariate logistic regression analysis. All variables that reached a P < = 0.05 in the univariate analysis will be included in the multivariate linear regression analysis. P <0.05 will be considered statistically significant.

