### Endpoints

The primary endpoint will be the number of RBC units transfused during the OLT procedure and in the 24 hour post-surgery period, starting from arrival at the ICU. Other efficacy endpoints are (measured during surgery and during the 24-hour period post-surgery):

• The number of transfused units of fresh-frozen plasma

• The number of transfused units of platelet concentrate

• Fibrinogen concentrate administration

• Estimated blood loss

• Antifibrinolytic drugs

• Crystalloids or colloids administered

• Other escape medication used

• Estimated ascites loss

Safety is a secondary endpoint, safety parameters recorded are:

• All (Serious) Adverse Events with special focus on thromboembolic events

• General and liver-specific laboratory parameters

• Lowest pH, Ca++, lactate, temperature (during and within the first 24 h after surgery)

• Troponin levels, ECG and hepatic vessel ultrasound results

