### Randomization and blinding

The surgical and anesthesiological team must remain blinded for the intervention during the entire duration of the trial. Randomization will be performed using an randomization website. We will stratify per center, and for patient age and gender. Randomization and preparation of the Investigational Medical Product (IMP), whether this is PCC or placebo, will be performed by an independent employee who is not involved in this trial, in the OLT or in post-operative care. The IMP will be delivered in a blinded syringe to the anaesthesiologist and administered by the anaesthesiologist.

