### Surgical and anesthesiological procedure

There is no change in surgical or anesthesiological procedure from the current practise in participating centers.

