### Statistics

#### Sample size

Based on experience in the participating centers, it is assumed that cirrhotic patients undergoing OLT have a mean transfusion requirement of 8 U RBC (SD = 4 U). This data was derived from a retrospective data analysis of transfusion requirements during OLT in the UMCG over 2008–2011. The sample size of this trial was chosen to detect a reduction of 2 units of RBCs with approximate 80% power. The following statistical formula for sample size calculation was used to determine the sample size. N = 16***σ***^2^ / d^2^.

With an expected 10% withdrawal or loss of study subjects we concluded that 70 patients in each group are required to demonstrate a difference between placebo and PCC administration.

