#### Interim analysis

One interim analysis will be performed by the trial statistician after 70 patients (50% of the sample size) have been included.

The Sponsor has chosen different boundaries for the different endpoints for the interim analysis, giving more significance to early unfavourable trends then to early beneficial trends. These boundaries are more used as guidelines rather than absolute rules.

For the efficacy endpoint, the O’Brien-Fleming sequential boundary will be used to correct for the instability of efficacy parameters at the beginning of the trial. For a total number of 2 planned statistical analyses and one planned interim analysis a Z-value of 3 with a P of 0.0027 will be used to determine statistical significance during the interim analysis. During the final analysis a Z-value of 2 and a P-value of 0.045 will be used to determine statistical significance.

For the safety endpoints, we have chosen to use the Pocock sequential boundary, dictating a Z-value of 2 and thus a P-value of 0.045 to determine statistical significance in harm between the two groups during the interim analysis as well as the final analysis.

Besides the efficacy and safety endpoint, during the interim analysis, sample size assumptions will be monitored based on the transfusion requirements in the placebo- group and if needed the sample size will be adjusted. Also, results from the blinded INR-measurements 30 minutes after intervention in de PCC-group will be used to determine whether the PCC-dose sufficiently lowers the INR in this patients group of whether the dose needs adjusting during the further conduct of this trial.

The trial may be stopped early due to one of the following situations:

– Unacceptable safety concerns: The analysis shows significant (serious) adverse events in the treatment group compared to the placebo group.

– The results on the endpoint between treatment-group and placebo group are inconclusive and it is expected that no significance will be reached.

– The interim analysis shows a clear benefit in the treatment group compared to the placebo group.

– In case new external information arises that convincingly answers the study question or raises serious safety issues.

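### Randomisation is stratified by centre, age and gender but the primary Mann–Whitney test ignores all three: still valid, but conservative and less powerful than an adjusted analysis if those factors are prognostic

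*Protocol article*

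**What the plan says.** All references are to the protocol article.

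- **Randomization and blinding:** "We will stratify per center, and for patient age and gender". No age cut-point, number of centres or block scheme is given.
- **Endpoints:** "The primary endpoint will be the number of RBC units transfused during the OLT procedure and in the 24 hour post-surgery period".
- **Statistical analysis:** "The Mann–Whitney U test will be used to determine a significant difference in transfusion needs between the 2 groups". The only regression named in that section looks for risk factors for bleeding and transfusion. It is not an adjusted comparison of the two arms.
- **Sample size:** "it is assumed that cirrhotic patients undergoing OLT have a mean transfusion requirement of 8 U RBC (SD = 4 U", and "The sample size of this trial was chosen to detect a reduction of 2 units of RBCs with approximate 80% power". The SD is attributed to a retrospective series at a single hospital, 2008–2011.
- **Interim analysis:** "During the final analysis a Z-value of 2 and a P-value of 0.045 will be used to determine statistical significance". This is the threshold used for the simulations below that apply |Z| > 2.
- **Surgical and anesthesiological procedure:** "There is no change in surgical or anesthesiological procedure from the current practise in participating centers".
- **Transfusion guidelines:** one policy is set for all centres, including red-cell transfusion at a haematocrit below 25%.

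**The concern.** Stratified randomisation makes the arms similar on the stratification factors. If a factor is prognostic, the true variance of the treatment contrast falls. An unstratified rank test still computes its null variance from the full spread of the outcome, including the part due to the factors that were balanced. Its standard error is then too large for the design, the true type I error drops below nominal, and some attainable power is not used.

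The article gives reasons to think centre could matter. Surgery and anaesthesia follow each centre's own practice. Transplantation technique and veno-venous bypass are recorded as variables. Other blood products and escape medication follow local procedures. At stake is efficiency in a trial of 140 patients planned at about 80% power.

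A smaller, related point is that the trial is sized on a difference in units, while a Mann–Whitney P-value does not express the effect in units.

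**Working it through.** **1. The plan's own figure.** Its formula gives N = 16σ²/d² = 16 × 4² / 2² = 64 per group. Allowing for 10% loss, 64 × 1.1 = 70.4 and 64 / 0.9 = 71.1, so the stated 70 per group is reproduced to within rounding. Evaluable patients: 70 × 0.9 = 63 per arm. The formula uses the overall SD and takes no credit for stratification.

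**2. Normal approximation, total SD 4, two-sided 5%.** Let R² be the share of outcome variance explained by the strata (an assumption; the article gives none).

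- SE used by the unadjusted test: 4 × √(2/63) = 0.713.
- True SE after stratified randomisation: 0.713 × √(1 − R²).
- Unadjusted power: Φ[(2 − 1.96 × 0.713) / (0.713√(1 − R²))].
- Adjusted power: Φ[2 / (0.713√(1 − R²)) − 1.96].
- True error of the unadjusted test: 2[1 − Φ(1.96/√(1 − R²))].

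Example at R² = 0.2, where the true SE is 0.637: unadjusted Φ(0.603/0.637) = 82.8%; adjusted Φ(3.137 − 1.96) = 88.1%; error 2.8%.

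| R² | Unadjusted power | Adjusted power | Unadjusted true error |
|---|---|---|---|
| 0 | 80.1% | 80.1% | 5.0% |
| 0.1 | 81.4% | 84.1% | 3.9% |
| 0.2 | 82.8% | 88.1% | 2.8% |
| 0.3 | 84.4% | 91.8% | 1.9% |

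**3. Simulation with the actual test.** Assumptions: 4 equal centres, 63 per arm, total SD 4, effect 2 units, |Z| > 2. Ranges are over two simulations.

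| Centre R² | Mann–Whitney true error | Mann–Whitney power | Rank regression with centre, power | Gap (points) |
|---|---|---|---|---|
| 0 | 4.0–4.5% | 76% | 77% | 0–1 |
| 0.1 | 3.4–3.7% | 77–78% | 80–81% | 2–4 |
| 0.2 | 2.5–2.7% | 79–80% | 84–85% | 4–6 |
| 0.3 | 1.3–1.6% | 79–82% | 89% | 7–10 |

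The 76% in the first row does not come from ignoring strata. It reflects the efficiency of a rank test under normality and the stricter final threshold.

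**4. If the SD of 4 is a within-centre SD.** The total SD then becomes 4/√(1 − R²): 4.22, 4.47 and 4.78 at R² = 0.1, 0.2 and 0.3. By the normal approximation with |Z| > 2, unadjusted power is Φ(2/0.713 − 2/√(1 − R²)); at R² = 0.2 this is Φ(2.806 − 2.236) = 72%. Simulated Mann–Whitney power is 76 / 74 / 71 / 65% at R² = 0 / 0.1 / 0.2 / 0.3, while rank regression with centre terms stays at 76–77%.

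**5. The form of the adjustment matters.** Power at 5%, N = 126, permuted blocks of 4 within strata:

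| Strata | R² | Mann–Whitney | Van Elteren | Rank regression |
|---|---|---|---|---|
| 12 | 0 | 77.1% | 74.7% | 77.1% |
| 12 | 0.1 | 79.5% | 79.0% | 81.3% |
| 12 | 0.2 | 78.9% | 82.7% | 84.1% |
| 24 | 0 | 77.0% | 69.4% | 74.6% |
| 24 | 0.1 | 78.3% | 74.0% | 78.9% |
| 24 | 0.2 | 78.6% | 78.6% | 82.2% |

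Van Elteren over many small cells can do worse than the plain test. Rank regression with a term for each of 24 cells also costs a little when the cells are not prognostic.

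**The case against.** The strongest reply is that nothing here is invalid. A conservative test cannot produce a false claim of benefit, the gain is about zero if the factors are not prognostic, and the article supplies no centre effect. The common transfusion policy is meant to limit centre differences in the endpoint itself, and the interim review may adjust the sample size. Adjusted analyses may also appear in an analysis plan that is not shown. All of this stands, and it is why the point concerns efficiency and is stated conditionally. It does not remove the mismatch, because the article itself names the primary test.

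A reader might infer more than the documents support:

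- **That the balance from stratification is wasted.** It is not. It still lowers the true variance of the contrast, and with total SD 4 unadjusted power rises slightly with R². Only the matching reduction in the test's own variance is forgone.
- **That power must fall below plan.** This follows only if 4 units is a within-centre SD. The single-hospital source makes that possible, but the article also appeals to experience across the participating centres.
- **That baseline INR belongs in the model because it drives eligibility and dosing.** The Background section reports studies in which PT and INR did not predict blood loss or transfusion during transplantation.
- **That baseline covariates are worth a definite number of extra patients.** The article gives no R² from which to calculate one.

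**Conclusion.** The point holds as a conditional efficiency issue of minor to moderate weight. The design and the named primary test do not match. If centre, age or gender predict red-cell units, the Mann–Whitney test is valid but conservative, and it forgoes about 2–4 points of power at R² = 0.1, 4–6 at 0.2 and 7–10 at 0.3, compared with an analysis that accounts for them. At R² = 0 the gap is 0–1 points. These figures rest on assumed values: 4 equal centres, 63 per arm, total SD 4, a 2-unit effect and |Z| > 2. Neither the number of centres nor the centre effect can be read from the article. If between-centre variation adds to the single-hospital SD, unadjusted power falls to about 74 / 71 / 65% at R² = 0.1 / 0.2 / 0.3, and adjustment protects against that.

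**What to change.** Make the primary test one that accounts for the stratification factors. The preferred form is a rank regression (rank-ANCOVA) of red-cell units on treatment with separate terms for centre, age and gender. A van Elteren test stratified by centre alone is an acceptable alternative. Do not stratify the test on the full centre × age × gender cross-classification, where small cells can cost more power than they recover.

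Keep the plain Mann–Whitney test as a sensitivity analysis. Report the difference in red-cell units with a 95% CI, so that the result can be read against the 2-unit reduction used for planning. If the unadjusted test is to stay primary, state why.

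The cost is a sentence or two of analysis wording and a few lines of code. The factors are known at randomisation, so no new data are needed. With few strata the statistical downside is negligible: in the simulations with 4 or 12 strata, rank regression lost no power when the strata were not prognostic. The change should be fixed before any unblinded comparison.

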### Intervention and dosage

The IMP will be administered during induction of anaesthesia, maximum 30 minutes prior to incision. The IMP, whether this is PCC or placebo will be administered according to the SPC of Cofact®/PPSB-D, intravenously and with a recommended infusion speed of 2 ml per minute. The dosage will be determined according to bodyweight, preoperative INR and target INR (≤1.5), as recommended in the SPC of Cofact® and as illustrated by Table 3. The same calculated dosage applies for the placebo.

**Table 3 T3:** Dosing of PCC according to INR and bodyweight to reach an INR < 1.5

**Body**	**Initial INR**												
**weight**	**4.8**	**4.2**	**3.6**	**3.3**	**3.0**	**2.8**	**2.6**	**2.5**	**2.3**	**2.2**	**2.0**	**1.8**	**>1.5**
50 kg	60	50	50	50	40	40	30	30	30	30	30	20	20
60 kg	70	60	60	60	50	50	40	40	40	30	30	20	20
70 kg	80	70	70	70	60	60	50	40	40	40	30	30	20
80 kg	90	90	90	80	80	70	60	50	50	40	40	30	20
90 kg	100	90	90	90	80	80	70	60	50	40	40	30	20
100 kg	100	100	100	90	90	80	70	70	60	50	50	30	20

The dosages are calculated based on the factor IX concentration in PCC (the above dosage refers to ml of PCC). Calculated amounts are rounded mathematically on multiples of 10 ml and an upper limit of 60 or 100 ml in total was set (see tables above). The target INR values are recommended by the Federation of Dutch Thrombosis Services and are of the same order as English and German recommendations.

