### Laboratory parameters

– Prior to the OLT, an INR measurement will be performed to check if the patient still meets the inclusion criteria. After administration of the IMP, no routine INR measurements will be performed by the anaesthesiologist during the course of surgery, since measuring the INR will likely unblind the anaesthesiologist for the intervention.

– A blinded INR measurement will be performed (see section ‘Additional Study Procedures’) by an independent assistant 30 minutes after administration of the intervention and will only be available for an independent researcher. These measurements will be used during the interim analysis.

– Troponin levels are recorded just before and after surgery at ICU admission and the day after surgery, and in case of a suspected event due to clinical symptoms or ECG abnormalities during routine testing according to routine clinical practice.

– During OLT other laboratory and coagulation measurements (with the exception of the PT) may be performed according to local practice.

– Post-operatively, laboratory measurements presented in Table 4 will be performed from day 1–7 in the first week which is currently common practice in participating centers. From the second week, these laboratory measurements are only obligatory on day 14 and 30 (within a 24 hour timeframe).

**Table 4 T4:** Laboratory parameters

**Hemostasis**	**Hematology**	**Clinical chemistry**	
Prothrombin Time	Hemoglobin (Hb)	C-reactive protein	Lactate dehydrogenase
Activated Partial Thromboplastin Time	Hematocrit	Glucose	Aspartate-aminotransferase
		Creatinine	Alanine-aminotransferase
Fibrinogen	Platelets	Urea	Alkaline Phosphatase
International Normalized Ratio	Leucocytes	Sodium	Albumin
		Potassium	Calcium
		gamma-glutamyltransferase	

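### Troponin and laboratory comparisons leave the pre-dose value unused: a minor loss of precision that costs nothing to recover, not an error in the plan

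*Protocol article*

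**What the plan says.** **Endpoints.** The safety parameters include "General and liver-specific laboratory parameters" and "Troponin levels, ECG and hepatic vessel ultrasound results".

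**When they are measured.** Under Laboratory parameters: "Troponin levels are recorded just before and after surgery at ICU admission and the day after surgery". Additional study procedures repeats this. Table 1 marks both the Lab row and the Troponin row in its first column (SEH), which stands before the surgical columns. The dose falls within those later columns: "The IMP will be administered during induction of anaesthesia, maximum 30 minutes prior to incision" (Intervention and dosage). The SEH values are therefore pre-dose. Afterwards, "Post-operatively, laboratory measurements presented in Table 4 will be performed from day 1–7 in the first week", with further panels on days 14 and 30.

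**How they are analysed.** The Statistical analysis section names the Mann–Whitney test for transfusion needs and Chi-square or Fisher tests for categorical data. For other continuous data it says only: "Intergroup continuous data will be analyzed with parametric or non-parametric analysis methods depending on the presence/absence of Gaussian distribution". Regression appears in that section only for finding risk factors for bleeding and transfusion, not for comparing the arms.

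**The concern.** The rule makes the shape of the distribution the only ground for choosing a method. It gives no role to the value that each patient had before dosing. A plain comparison of post-operative values carries all the between-patient spread that was already there on admission. To the extent that the pre-dose value predicts the later one, this spread is avoidable noise.

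What is at stake is the precision of secondary safety comparisons. The article's secondary objective lists laboratory measurements, beside adverse event surveillance, as a means of monitoring safety. The Interim analysis section says that unfavourable trends should weigh more than favourable ones. The interim look has only about 35 patients per arm, so precision is scarcest there.

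**Working it through.** **Inputs**
- From Sample size: SD 4 U, difference 2 U, 10% loss, 70 per group. These concern red cell units; the article gives no size calculation for laboratory values or troponin.
- From Interim analysis: a look after 70 patients (35 per arm), and P = 0.045 for safety endpoints at both analyses.
- Assumed: the pre/post correlation r, which the documents do not give, shown from 0 to 0.7.
- Assumed: a harmful shift of 0.5 SD, the same standardised size as the primary effect (2/4 = 0.5).

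**Step 1: the plan's own figure.** N = 16σ²/d² = 16 × 16 / 4 = 64 per group. The normal-approximation formula gives 63, and 63/0.9 = 70. Starting from 64 gives 64 × 1.1 = 71 or 64/0.9 = 72 after rounding up. The stated 70 is reproduced to within 2 patients. Evaluable patients per arm are 70 × 0.9 = 63.

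**Step 2: effect of adjustment.** With the pre-dose value as covariate:
- variance factor = 1 − r²
- equivalent patients per arm = 63/(1 − r²)
- shift detectable with 80% power, in SD = (2.005 + 0.842) × √(2/63) × √(1 − r²)
- power for 0.5 SD = Φ(0.5 / [√(2/n) × √(1 − r²)] − 2.005)

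| r | 1 − r² | Equivalent n per arm | Detectable shift (SD) | Power, final (63 per arm) | Power, interim (35 per arm) |
|---|---|---|---|---|---|
| 0 (same as unadjusted) | 1.00 | 63 | 0.507 | 78.9% | 53.5% |
| 0.2 | 0.96 | 66 | 0.497 | 80.5% | 55.2% |
| 0.3 | 0.91 | 69 | 0.484 | 82.6% | 57.5% |
| 0.5 | 0.75 | 84 | 0.439 | 89.2% | 65.9% |
| 0.7 | 0.51 | 124 | 0.362 | 97.3% | 82.2% |

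At the general 5% level the picture is the same: 80.1% unadjusted at the final analysis, and 83.7%, 90.0% and 97.6% at r = 0.3, 0.5 and 0.7.

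**Step 3: skewed data.** A simulation with log-normal values, 63 per arm, a 0.5 SD shift on the log scale, alpha 0.045 and 3,000 runs per r compared Mann–Whitney with rank ANCOVA. Power was about 77% and 77% at r = 0, 76% and 78% at 0.2, 77% and 80% at 0.3, 76% and 86% at 0.5, and 77% and 96% at 0.7. Adjustment costs essentially nothing when the pre-dose value is uninformative.

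**Step 4: the obvious alternative.** A test on change from baseline has variance factor 2(1 − r), which exceeds 1 whenever r < 0.5. At r = 0.3 it is 1.4, and power at 63 per arm falls to 64.3%, below the unadjusted 78.9%. The pre-dose value should enter as a covariate, not be subtracted.

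**The case against.** The strongest reply is that the article names no test for safety data. ANCOVA is a parametric method and rank ANCOVA a non-parametric one, so the fix fits within the quoted sentence. Covariates for secondary laboratory data are also commonly left to the full protocol or analysis plan, neither of which is shown. This stands in part: a reader may not conclude that the trial has ruled out adjustment. The sentence is nevertheless a stated rule. It stands beside named two-sample tests, and regression is kept for another purpose, so an unadjusted comparison is its natural reading.

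A reader might infer that chance imbalance at baseline makes the unadjusted result misleading. It does not: under randomisation the test's type I error already allows for chance imbalance.

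The size of the gain is also open to challenge, and this stands:
- The documents report neither the pre-operative spread of these tests nor r.
- The liver is replaced between the two samples, so r may be low for liver-derived values.
- Under Transfusion guidelines, red cells are given at a hematocrit below 25%, and phlebotomy is provided for when it stays above 30% after surgery. Platelet counts below 50,000/mm³ with ongoing bleeding permit platelet concentrate. Management thus constrains hemoglobin, hematocrit and platelets.
- Table 2 excludes patients on dialysis and those with documented coronary artery disease, which may narrow the baseline range of creatinine and troponin.

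Pre-dose coverage is uneven too. Troponin is confirmed in the prose. For the panel, the prose names only one pre-operative test ("Prior to the OLT, an INR measurement will be performed to check if the patient still meets the inclusion criteria"), and the rest depends on the Lab mark in Table 1. No pre-dose value is stated for lowest pH, lactate or temperature.

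**Conclusion.** The point holds as a minor efficiency improvement. As most naturally read, the rule for continuous data leaves unused a pre-dose value that is collected for troponin and, by Table 1, for the laboratory panel. For a 0.5 SD shift at the final analysis the cost is about 2 power points at r = 0.2, 4 at 0.3, 10 at 0.5 and 18 at 0.7, and near zero where r is near zero. All of these rest on an assumed r, and the two larger gains need r of 0.5 or more.

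A stronger reading, that the trial gives away its sensitivity to harm, is not supported. Interim analysis and Premature termination of the trial word the harm criterion in terms of (serious) adverse events. The declared safety focus is thromboembolic events, which are compared as events. Neither would change with this adjustment. The unadjusted comparison remains valid, and nothing in the section is wrong in itself.

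**What to change.** In Statistical analysis, add one sentence: post-operative troponin, and those Table 4 parameters for which a pre-dose value is recorded, are compared between arms by ANCOVA with the pre-dose value of the same test as covariate. The scale is logarithmic, or ranks where values are skewed or often below the detection limit. Report the arm contrast with its 95% confidence interval; on the log scale this is the ratio of PCC to placebo. Do not use change scores. Lowest pH, lactate and temperature stay unadjusted.

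The cost is analysis wording only. On the Table 1 schedule the values are already being collected, so no new samples, visits or patients are needed, and the planned software can fit the model. The sentence should be fixed before unblinded data are seen, so that the choice of covariate cannot depend on the results.

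### The exploratory risk-factor analysis is called logistic in one sentence and linear in the next, and its univariate P ≤ 0.05 screen makes the 'independent' factors it reports unreliable

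*Protocol article*

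**What the plan says.** All of this stands in the Statistical analysis section of the protocol article.

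- Model, first sentence: "Independent risk factors for bleeding diathesis and transfusion during OLT will be identified using uni- and multivariate logistic regression analysis".
- Model and entry rule, next sentence: "All variables that reached a P < = 0.05 in the univariate analysis will be included in the multivariate linear regression analysis".
- Level for the final model: "P <0.05 will be considered statistically significant", in line with "Two-sided tests using the 5% critical level will be used throughout".
- Multiplicity: "If required, appropriate corrections for multiple comparisons will be applied".
- Treatment comparison, stated separately: "The Mann–Whitney U test will be used to determine a significant difference in transfusion needs between the 2 groups".

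The risk-factor sentences give no scale for bleeding diathesis or transfusion. Under Endpoints, transfusion is a count: "The primary endpoint will be the number of RBC units transfused during the OLT procedure" (continued into the first 24 hours on the ICU).

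**The concern.** Logistic regression takes a binary outcome and linear regression a quantitative one, so the two sentences cannot describe the same fit. Whoever runs the analysis must choose between them, and the text as it stands would allow that choice after the data are seen.

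The entry rule is a separate weakness. A variable enters because its P-value in these data is at most 0.05, and it is then judged at 0.05 in the same data. The second P-value does not allow for the selection. The rule can also discard a factor whose contribution shows only once others are in the model. At stake is whether the factors published as independent predictors of transfusion can be believed. The comparison of PCC with placebo is not at stake.

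**Working it through.** **1. The two sentences side by side.** The first assigns logistic regression to both the univariate and the multivariable step, and to both named outcomes. The second assigns linear regression to the multivariable step. No split by step or by outcome makes both true, and nothing elsewhere in the article reconciles them.

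**2. The plan's own figure.** The risk-factor text has no figure of its own, so the relevant one is the number of patients. The Sample size section gives SD 4, difference 2 and N = 16σ²/d². This is 16 × 16 / 4 = 64 per group. With 10% loss, 64 × 1.1 = 70.4, or 64 / 0.9 = 71.1, rounded up to 72. The stated 70 per group is reproduced to within two patients, so 140 in total is used below.

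**3. What the screen does to noise variables.** The article does not say how many candidate factors there are; 10 and 20 are assumed, all unrelated to the outcome and to each other. By formula, the chance of at least one result at P ≤ 0.05 is:

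- 10 candidates: 1 − 0.95^10 = 0.40
- 20 candidates: 1 − 0.95^20 = 0.64

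The full two-step procedure was then simulated with N = 140. Counts were negative binomial with mean 8 and SD 4 (size 8² / (16 − 8) = 8). The logistic version splits the count at its median, which is an assumption because the article gives no cut-point. There were 1,500 runs for linear and 300 for logistic.

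| Candidates | Model | At least one false factor | Screened-in noise variables still significant |
|---|---|---|---|
| 10 | linear | 0.40 | 94% |
| 10 | logistic | 0.35 | 91% |
| 20 | linear | 0.65 | 86% |
| 20 | logistic | 0.63 | 86% |

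The false-factor rate after both steps is close to the rate for the screen alone, so the multivariable step removes little.

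**4. Does the choice of model matter?** One factor, same count distribution, N = 140, 1,000 runs per row:

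| Log-rate slope per SD | Linear | Logistic, median split | Negative binomial |
|---|---|---|---|
| 0 (type I error) | 0.049 | 0.048 | 0.050 |
| 0.10 (power) | 0.65 | 0.45 | 0.66 |
| 0.12 (power) | 0.79 | 0.58 | 0.80 |

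Linear and negative-binomial regression are nearly equal here. Splitting the count costs about 20 points of power. The two models that the article names therefore give materially different analyses.

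**The case against.** The strongest reply is that this is a one-word slip in an analysis that is neither a stated objective nor a listed endpoint, in an article that condenses a fuller protocol. Much of that stands. It settles the severity, and it means that the absent cut-point and covariate list are not faults in themselves. It does not remove the contradiction, because both models and the entry threshold are stated text.

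A second reply is that the false-factor rates are mostly plain multiplicity and rest on an assumed number of candidates. That is fair. A prespecified model with seven null terms, each tested at 0.05, would still give 1 − 0.95^7 = 0.30. What belongs to the screen itself is the second test that does not confirm, and the loss of factors that matter only jointly.

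Three stronger readings might be inferred, and the documents do not support them:

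- That linear regression is unfit for the outcome. Under the protocol's mean of 8 and SD of 4 it held its type I error at 0.049 and nearly matched negative-binomial power. Heavier skew or many zeros could change this, but the article states neither.
- That a fixed share of the information is lost. For a normal outcome a median split keeps 2/π = 64%, so 140 patients would count as about 89. The article nowhere plans a median split, so this only illustrates one way of running the logistic version.
- That the screen could drop the randomised treatment and so threaten the trial's conclusion. Treatment is compared by a separate Mann–Whitney test, and nothing says that its effect will be estimated through this regression.

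**Conclusion.** The point holds, at minor severity. The contradiction over model and outcome scale rests on the text alone and needs no assumption. The unreliability of the 'independent' factors follows from the stated screen. Its size, 35% to 40% with 10 candidates and 63% to 65% with 20, depends on the assumed number of independent null candidates, complete data on 140 patients and negative-binomial counts with the protocol's mean and SD. The power loss of about 20 points applies only if the count is split at its median. The primary test, the sample size and the interim boundaries do not depend on any of this.

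**What to change.** Rewrite the two sentences.

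1. **One model, one outcome.** Preferably analyse RBC units as a count, for example by negative-binomial regression reporting rate ratios with 95% CI. Linear regression would perform similarly under the assumed mean and SD. Do not dichotomise the count. If bleeding diathesis is kept as an outcome, define it and give it its own model.
2. **No univariate screen.** Use a short list, fixed in advance, of covariates known before the study drug is given: treatment arm; the stratification factors centre, age and gender; and a few baseline values such as INR, haematocrit and platelets. Leave out values that may not be complete by then, such as cold-ischaemia time, because events after dosing could influence them. Keep every listed covariate in the model whatever its P-value.
3. **Label the analysis exploratory**, and report estimates with intervals rather than a list of significant factors.

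This is a change of wording and needs no new data. The real cost is that 140 patients support only a short list, particularly if centre takes several terms, so fewer candidate factors can be examined.
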